#### Economic evaluation

A cost-effectiveness analysis will be conducted alongside the clinical trial. Two complementary cost-effectiveness analyses will be performed, namely, a within-trial evaluation where cost and health effects of individual patients are limited to the 1-year follow-up period of the trial and a decision model approach where effects are modelled to incorporate longer-term impacts of the intervention.

The primary outcome of the economic evaluation is the ICER of RA compared with LA in AVF creation expressed in cost per QALY (£/QALY). All intervention resource use and access-related resource use will be derived from the secondary outcome measures and unit costs applied to all resource use estimates informed, where possible, from standard UK sources. A bottom-up approach will be used to estimate the costs associated with the two anaesthesia procedures. Effects will be captured at the individual patient level and QALYs will be derived by combining overall survival with utility weights derived from the EQ-5D questionnaire values obtained at the preoperative time, at 3 and 12 months after treatment.

A discrete-time state-transition Markov model will then be used to assess the long-term economic impact of the intervention beyond the trial period, with each cycle consisting of relevant events (ie, maturation/functional patency, failure, complications, reintervention, alternative access, adverse events (AEs) and death). Events will be driven by transition probabilities within the model, being informed partly by within-trial data in the short-term (ie, up to 1 year) and other sources (literature, electronic health records, etc) in the long-term (ie, beyond 1 year).

### Retention/withdrawal criteria

Participants may voluntarily withdraw from the study at any time. However, due to the nature of the intervention, it is impossible to change the allocated treatment once the anaesthetic procedure has been performed. Follow-up visits will be timed to coincide with dialysis sessions to minimise follow-up burden and to promote trial retention.

### Data collection and data management

Study specific data, which is non-identifiable, will be collected on the electronic case report form (eCRF) using a unique patient identifier for reporting. Only the study site will have access to the identifiable information to maintain participant confidentiality. Pseudoanonymised data entered into the eCRF will be managed and stored by the RCB. The RCB systems are fully validated in accordance with industry and regulatory standards and incorporate controlled access security. Data integrity is assured by strictly controlled procedures, including secure data transfer procedures. A computer database will be constructed specifically for the trial data and will include range and logic checks to prevent erroneous data entry. Independent checking of data entry will be periodically undertaken on small subsamples. The trial statistician will also regularly check the balance of allocations by stratification variables.

All essential documents will be archived in a secure commercial vault for a minimum of 5 years after completion of the trial. Trial data will be stored under controlled conditions for at least 10 years after closure. During this period, all data will be accessible to the competent authorities and the sponsor for audit and monitoring purposes with suitable notice.

### Sample size

A total of 566 subjects (283 per arm) are required to detect a 15% difference in the primary outcome measure with 5% significance level and 90% power, assuming that 15% of subjects will be lost to follow-up, will change RRT modality or die.

Fifteen per cent is considered to be the minimum clinically important difference between the two cohorts. It is a conservative estimate of the 19% difference in 1-year unassisted functional patency observed in the results from our single-centre RCT and is the magnitude of difference considered appropriate by experts following independent review of the protocol by the UK Renal Trials Network (UKRTN).^12^ UKRR data indicate that 47% of incident patients currently commence HD via an AVF/AVG.^6^ A 15% increase in functional patency would allow the renal association target of 60% to be achieved.

### Statistical analysis plan

All statistical analyses will primarily be performed according to the intention-to-treat principle. However, additional analysis will be prespecified to address ‘failed blocks’ (eg, per-protocol, as treated, and complier-average causal effects analyses). Baseline demographics will be summarised by treatment group without formal statistical comparison. The primary outcome will be analysed using logistic regression, adjusting for stratification variables used at randomisation and the treatment group assigned. The treatment effect will be reported with a 95% CI for the OR and p value also reported. Time to loss of functional access will also be analysed using survival analysis regression methods. Similarly, for each of the secondary outcomes, analyses will be conducted using appropriate regression methods reporting the treatment effects, 95% CIs and p values. Safety data including the number of adverse events (AEs) and serious adverse events (SAEs) will be reported overall and by study arm, where no formal statistical testing will be carried out.

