### Recruitment

Potentially eligible participants will be identified from vascular access and/or ‘predialysis’ (low-clearance) clinics and theatre waiting lists by the clinical team. A vein mapping ultrasound (US) will be performed to ensure minimum vessel characteristics. We anticipate 12–20 centres recruiting an average of two patients/centre/month. Recruitment is due to commence May 2021 and is anticipated to take 2 years. Preliminary results are expected late 2024.

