### Inclusion criteria

Inclusion criteria are outlined in box 1.

Box 1Inclusion and exclusion criteriaInclusion criteriaAll adult patients (≥18 years old) with kidney failure requiring kidney replacement therapy or chronic kidney disease stage IV or V referred for primary radiocephalic fistula or brachiocephalic fistula creation.Exclusion criteriaGeneralPatients unable or unwilling to provide informed consent.Patient preference for general or alternative anaesthesia.Active infection at surgical or anaesthetic site.Access specificPrevious ipsilateral AVF creation (a previous attempt at distal AVF creation which fails immediately is not considered a contraindication, but any distal access which has previously run sufficiently to mature the outflow vein or proximal revision of an existing AVF is considered a contraindication).Known ipsilateral cephalic arch or central venous stenosis (even if previously treated).USS evidence of stenosis in inflow artery.Radial or brachial artery of <1.8 mm diameter and/or cephalic vein of <2 mm at the wrist or <3 mm at the elbow (with tourniquet) on preoperative USS.^29^
Contraindications to anaesthetic agents/ techniqueAllergy to local anaesthesia or any excipient agents.Acquired or inherited coagulopathy (including warfarin/heparin/novel oral anticoagulant use where it has not been possible to stop the anticoagulation in anticipation of surgery) and/or platelets of <75 or International Normalised Ratio (INR) of >1.4.^30^
Significant pre-existing neurological disorder affecting the upper limb.Weight of <45 kg.

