### Allocation

A central randomisation facility (interactive web response system) at the Robertson Centre for Biostatistics (RCB), University of Glasgow, will randomise patients 1:1 to the intervention group (RA) or the comparator group (LA). The randomisation list will be created by a computer-generated program using a method of permuted blocks stratified by centre, dialysis status (predialysis/HD) and site of AVF (RCF/BCF). Randomisation will take place at a patient, not centre, level to minimise bias from variation in surgical and dialysis practice. The randomisation list, the program that generated it and the random seed used will be stored in a secure network location, accessible only to those responsible for provision of the randomisation system. Clinicians responsible for delivering the perioperative care will perform the web-based randomisation.

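### Optional gain: the valid primary logistic model could also adjust for the preoperative artery and cephalic vein diameters that eligibility already requires

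*Protocol article*

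**What the plan says.** The Statistical analysis plan section states the covariate set of the primary analysis: "The primary outcome will be analysed using logistic regression, adjusting for stratification variables used at randomisation and the treatment group assigned". It also states the effect measure: "The treatment effect will be reported with a 95% CI for the OR and p value also reported". Under Allocation, randomisation is "stratified by centre, dialysis status (predialysis/HD) and site of AVF (RCF/BCF"), so the model contains treatment, centre, dialysis status and fistula site.

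Under Recruitment, "A vein mapping ultrasound (US) will be performed to ensure minimum vessel characteristics". Box 1 (Inclusion criteria) turns this into an exclusion: "Radial or brachial artery of <1.8 mm diameter and/or cephalic vein of <2 mm at the wrist or <3 mm at the elbow". Eligibility therefore cannot be decided without these diameters. Under Outcomes, the ultrasound part of the primary outcome in predialysis patients uses a 4 mm diameter target together with a flow criterion.

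**The concern.** A baseline measurement that is needed for eligibility, and that is of the same kind as one component of the outcome in predialysis patients, is not in the primary model. The minimum diameters are floors, so vessel size still varies above them within each fistula site. Adjusting for site captures only part of that variation.

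If diameter predicts patency, leaving it out gives up some power and lets a chance imbalance between arms pass into the estimate. The primary covariate set is named in the protocol and is not left open. Adding a term after unblinding would be a departure from the published analysis, so the choice has to be made beforehand.

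**Working it through.** **1. The plan's own figure.** The Sample size section plans 566 participants, 283 in each arm, for a 15-point difference, with the significance level at 5% and power at 90%. Attrition enters as follows: "assuming that 15% of subjects will be lost to follow-up, will change RRT modality or die". It gives no control rate and does not say whether the test is two-sided; two-sided is assumed here.

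The two-proportion formula is n = [z(0.975)·√(2p̄q̄) + z(0.90)·√(p₁q₁ + p₂q₂)]² / 0.15². The continuity correction is n′ = (n/4)·[1 + √(1 + 4/(0.15n))]².

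- At 50% against 65%: n = 227 and n′ = 240. Then 240/0.85 = 282.4, rounded up to 283 per arm, or 566 in total. This is exact. 35% against 50% gives the same.
- At 47% against 62% (47% is the registry figure in the same section, for starting haemodialysis by fistula or graft): n′ = 243 and the total is 572.

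The stated size is reproduced and takes no credit for covariate adjustment. With 240 evaluable per arm, an unadjusted comparison of 47% with 62% has about 91% power.

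**2. What adjustment adds.** The documents give no prognostic strength for diameter, so a range is assumed: an odds ratio per SD of 1.0 to 2.0. Each scenario has 10,000 simulated trials with 240 per arm. The logistic outcome is calibrated to the stated marginal rates. Two binary strata are in the fitted model, and one standard normal index stands for both diameters. Each cell shows the result without → with the index.

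| Rates | OR per SD | Power, % | Mean log OR | Mean SE of log OR | SD of risk difference |
|---|---|---|---|---|---|
| 47 v 62 | 1.0 | 91.2 → 91.2 | 0.615 → 0.617 | 0.1868 → 0.1872 | 0.0449 → 0.0450 |
| 47 v 62 | 1.25 | 91.0 → 91.5 | 0.617 → 0.626 | 0.1868 → 0.1884 | 0.0456 → 0.0454 |
| 47 v 62 | 1.5 | 91.1 → 91.9 | 0.614 → 0.639 | 0.1868 → 0.1911 | 0.0450 → 0.0443 |
| 47 v 62 | 2.0 | 91.3 → 93.6 | 0.615 → 0.683 | 0.1868 → 0.1979 | 0.0451 → 0.0429 |
| 50 v 65 | 2.0 | 91.6 → 93.9 | 0.626 → 0.695 | 0.1884 → 0.1995 | 0.0447 → 0.0427 |
| 35 v 50 | 2.0 | 91.6 → 93.9 | 0.622 → 0.691 | 0.1883 → 0.1994 | 0.0447 → 0.0426 |

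Take the 47% v 62% row at OR 2.0. The SE of the log OR rises by 0.1979/0.1868 − 1 = 5.9%. The log OR moves further from zero, by 0.683/0.615 − 1 = 11.1%. Their ratio therefore goes from 3.29 to 3.45, and that is where the power comes from. On the risk-difference scale the estimate does become more precise: 1 − 0.0429/0.0451 = 4.9% at OR 2.0 and 1 − 0.0443/0.0450 = 1.6% at OR 1.5.

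**3. Chance imbalance.** With 240 per arm, the standardised difference between arms in a baseline variable has SD √(2/240) = 0.091. The edge of its 95% range is 1.96 × 0.091 = 0.18 SD. An imbalance of that size would move the log OR by about 0.18 × ln 1.5 = 0.07 or 0.18 × ln 2 = 0.12. The target for 47% against 62% is ln[(0.62/0.38)/(0.47/0.53)] = 0.61.

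**Limits.** One index replaces two diameters. Centre effects are left out, and the strata in the simulation carry no effect on the outcome. The true gain beyond fistula site is unknown.

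**The case against.** The strongest reply is that nothing here is wrong. Adjusting for the randomisation strata is standard and valid, the trial already has about 91% power under its own assumptions, and further covariates are often settled in a statistical analysis plan, which is not shown. That stands, and it is why the point is optional. What remains is that the protocol names the primary covariate set, so an addition has to be made deliberately and before unblinding.

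The gain may also be smaller than the table suggests. Small vessels are excluded, fistula site is already in the model and the vein threshold differs by site. The Fistula surgery section lets the surgeon choose other veins or a proximal fistula, so the scanned vessel may not be the one used. All of this weakens the prognostic strength one should assume. It does not make adjustment invalid, because the scan precedes randomisation.

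A reader might infer three stronger claims that the documents do not support:

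- *That precision is being given up at no cost.* The planned effect measure is an odds ratio, and the SE of its logarithm rises on adjustment. The odds ratio also becomes conditional on diameter, and a functional form and a missing-value rule are needed.
- *That the protocol treats vessel size as decisive for patency, or stores it as a number.* It sets an eligibility floor only, and the data collection section lists no such field.
- *That quality-of-life and QALY analyses omit the baseline value.* The Economic evaluation section uses "utility weights derived from the EQ-5D questionnaire values obtained at the preoperative time, at 3 and 12 months after treatment", so a preoperative value is collected. The unspecified regression methods for secondary outcomes do not exclude a baseline term, and the QALY regression is commonly left to an analysis or health economics plan.

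**Conclusion.** The planned primary analysis is sound. It leaves unused a baseline measurement that eligibility requires, and adding it would be a modest improvement of low severity. For an assumed odds ratio per SD of 1.0 to 2.0, the gain is about 0 to 2.5 points of power and up to about 5% off the SD of the standardised risk difference. Chance imbalance in diameter would no longer affect the estimate. If diameter does not predict patency in the eligible population, power is essentially unchanged. The size rests on that assumed strength, on 240 evaluable per arm, and on control rates between 35% and 50%.

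**What to change.** Before unblinding:

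- Add artery diameter and cephalic vein diameter, from the preoperative scan at the planned fistula site, as continuous covariates in the primary logistic model beside the stratification factors.
- State their functional form (for example, linear in mm) and a simple rule for missing values (for example, the overall mean).
- Report a standardised risk difference with 95% CI beside the odds ratio. This is the scale on which the trial was sized and on which precision improves.
- Confirm that both diameters are captured as numbers on the eCRF.

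The cost is analysis-plan wording and, if the values are not already captured, two eCRF fields filled from scans that are done anyway. The odds ratio must then be described as conditional on diameter as well as on the strata.

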### Interim analysis and early termination criteria

A 4-month internal pilot will be employed, principally to assess feasibility of recruitment. Stop–go (traffic light) criteria for continuance to the full trial will be used:

Red: stop if <50 patients are recruited or if <5 centres are open to recruitment.Amber: enrol more centres if between 48 and 95 patients are recruited.Green: continue within existing parameters if >95 patients are recruited.

If there is failure of adherence to trial protocol in >20% of participants or significant safety concerns are raised by the IDMC, the trial will not progress beyond the pilot phase. In the event that the trial was to be terminated following the internal pilot, all patients would be followed up until the end of trial.

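### The red and amber limits of the internal pilot overlap, so 48 or 49 recruits means both stopping the trial and opening more centres

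*Protocol article*

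**What the plan says.** All the limits are in the protocol article under Interim analysis and early termination criteria. The pilot is introduced thus: "A 4-month internal pilot will be employed, principally to assess feasibility of recruitment". Three categories then decide whether the trial goes on:

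- "Red: stop if <50 patients are recruited or if <5 centres are open to recruitment"
- "Amber: enrol more centres if between 48 and 95 patients are recruited"
- "Green: continue within existing parameters if >95 patients are recruited"

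The planning figures behind recruitment are in the Recruitment section: "We anticipate 12–20 centres recruiting an average of two patients/centre/month", and "Recruitment is due to commence May 2021 and is anticipated to take 2 years". Nothing in the article says which category prevails if a count meets two of them. The section on trial management and audit leaves any decision on early termination to the steering committee with the sponsor and funder.

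**The concern.** A stop-go rule should map every possible result to one action before the result is known. Here the red limit lies above the amber floor, so the two categories share some counts. For those counts the rule gives two incompatible instructions: end the trial, or expand it. Whoever applies the rule would then have to choose with the count already in front of them, and the criteria exist to prevent that. What is at stake is whether a 566-patient trial proceeds if its pilot recruitment falls on one of the shared values.

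**Working it through.** **Inputs.** Pilot length: 4 months (Interim analysis section). Planned centres: 12 to 20, each averaging 2 patients a month (Recruitment section). Limits: red below 50 patients or below 5 centres, amber 48 to 95, green above 95 (Interim analysis section).

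**Step 1: reproduce the limits from the planned rate.** Expected recruits = centres x 2 x 4, with all centres open throughout.

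- 12 centres, the planned minimum: 12 x 2 x 4 = 96, the first green count.
- Half of that: 96 / 2 = 48, the amber floor. Equivalently, 6 x 2 x 4 = 48.
- A red limit of 50 would need 50 / 8 = 6.25 centres, so it does not come from the same calculation.

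**Step 2: classify each count, with at least 5 centres open.**

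| Recruits | Red (<50) | Amber (48 to 95) | Green (>95) |
|---|---|---|---|
| 47 | yes | no | no |
| 48 | yes | yes | no |
| 49 | yes | yes | no |
| 50 | no | yes | no |
| 95 | no | yes | no |
| 96 | no | no | yes |

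The amber-green boundary is clean. The red-amber boundary overlaps at exactly two counts. Reading the amber range as excluding its end points does not help: 49 would still be in both categories, and 95 would then be in none.

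**Step 3: how likely is a shared count?** The article gives no site-opening schedule, so the expected pilot total is an assumption and is shown as a range. If the total is Poisson with mean m, then P(48 or 49) = e^(-m) x (m^48/48! + m^49/49!).

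| Expected total m | One way to reach it at 2 per centre per month | P(48 or 49) |
|---|---|---|
| 40 | 5 centres, all 4 months | 4.9% |
| 48 | 6 centres, all 4 months; or 12 centres open 2 months on average | 11.4% |
| 56 | 7 centres, all 4 months | 6.8% |
| 64 | 8 centres, all 4 months; or 16 centres open 2 months on average | 1.5% |
| 80 | 10 centres, all 4 months; or 20 centres open 2 months on average | 0.009% |
| 96 | 12 centres, all 4 months | about 0.000007% |

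The probability is highest when the expected total lies on the boundary itself, so 11% is close to the maximum.

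**The case against.** **Little is affected.** Recruitment counts are not outcome data, so settling the matter at the time introduces no bias in the treatment effect, and the decision already has a named owner. Both statements are correct. They limit the severity of the point, but the text still gives two instructions for the same count. Condensation of the full protocol into an article is no answer either, because the article prints the whole numerical rule and the contradiction is between two printed limits.

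**The source of the slip is not documented.** This stands. The article does not say how the limits were derived. That 96 and 48 fit the planned rate and 50 does not is suggestive only, and raising the amber floor to 50 would remove the overlap equally well.

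**Stronger readings that the document does not support.** A reader might infer that red also contradicts the centre criterion beside it, since 5 centres at the planned rate give 5 x 2 x 4 = 40 recruits and 6 give 48, both below 50 although at least 5 centres are open. This is not an error. The two red limits are joined by *or*, so each is sufficient to stop, and having 5 centres open was never stated to guarantee continuation. The result also fits the plan: over the 24 months of recruitment, 5 or 6 centres at 2 a month give 5 x 2 x 24 = 240 or 6 x 2 x 24 = 288 of the 566 required. For the same reason there is no case for replacing the rule with recruits per open centre-month, which would pass a 5-centre trial unable to reach its target in the planned time. A reader might also take 11% as the typical chance of meeting the overlap. It holds only if the expected total is about 48, and the documents give no opening pattern that implies this.

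**Conclusion.** The rule is wrong as written, and the severity is minor. The overlap at 48 and 49 follows directly from the printed limits and needs no assumption. The inference that red was meant to be below 48 is plausible but unproven. The practical exposure depends on the expected pilot total and on Poisson variation around it. It ranges from about one chance in nine when that total is near 48 to practically none when 12 centres recruit to plan throughout. The consequence is limited to the progression decision at those two counts. Type I error, power and the primary analysis do not depend on it.

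**What to change.** Make the three categories mutually exclusive before the pilot decision is taken. Either of these does so:

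- red below 48, amber 48 to 95, green above 95, which agrees with the planned rate; or
- red below 50, amber 50 to 95, green above 95.

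The sponsor should confirm which was intended. The centre limit can stay as it is. If the pilot decision has already been made, record which recruitment limit was applied. The cost is one line of protocol wording, with no extra patients and no change to the analysis.
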